#### Instrumented Motor-Cognitive Dual Tasking (Physilog by GaitUp, NeuroVocalix by Cambridge Cognition, and Portable Electroencephalogram by Neurosteer)

The participants were asked to perform a series of motor and cognitive tasks in isolation (single task) and concurrently (dual task). The motor task comprised walking at a self-selected pace for 1 minute. The cognitive task comprises counting backward in 2 difficulty levels (in steps of 1 and 3). The sequence and duration of the tasks are presented in Figure 5. To measure motor performance, 2 wearable inertial sensors (Physilog 5 by GaitUp) measuring acceleration (accelerometer; sampling frequency 128 Hz) and angular velocity (gyroscope; sampling frequency 128 Hz) were attached to participants’ feet. Using GaitUp’s algorithm, which has been validated in several patient populations [26-28], gait parameters such as but not limited to gait speed, step and stride length, step and stride time, and step and stride variability were extracted. To measure cognitive performance, a small microphone (Wireless GO; RØDE) was attached to participants’ clothes, which recorded the counting. Voice recordings were streamed to the NeuroVocalix web-based platform by Cambridge Cognition. The voice recordings will be analyzed for counting rate, number of errors, and correct counts, as well as vocal features during counting such as the length of pauses between numbers, energy, and pitch as features of the frequency spectrum. In addition, a wearable, single-channel electroencephalogram by Neurosteer was placed on the participants’ foreheads to measure brain function. The single- and dual-task phases will be used to compare the frontal brain activity between tasks and correlate to measures of cognitive load such as frequency-band power and Neurosteer’s brain activity biomarkers [29].

**Figure 5 figure5:**
[figure not shown]
Task flow during dual tasking paradigm testing.

#### Neurosteer Auditory Cognitive Assessment

This test is a cognitive assessment based on auditory stimuli used to probe cognitive functionality. The testing includes auditory detection, n-back, auditory memory tasks, and resting state tasks. The detection and n-back tasks introduce different sequences of musical instrument melodies, eliciting participant responses. The detection task is used to test attention, inhibition response, and accuracy, whereas the n-back measures working memory. The memory tasks include statement recollection, mental clock imagery, and word recall. These are meant to test semantic memory, working memory, and memory consolidation and retrieval. Participants performed a 10-minute assessment while being recorded with a single-channel, medical-grade electroencephalogram. A total of 3 cognitive load levels (high, low, and rest) were used during the tasks and were correlated with behavioral performance and brain activity. The biomarkers extracted by the system were calculated using harmonic analysis and machine learning methods.

#### Winterlight Speech Assessment

Winterlight Speech Assessment was developed to record and analyze naturalistic speech using a tablet app. For the MEDIA study, each assessment included 2 picture description tasks in which participants were prompted to describe drawings of scenes presented on the tablet’s screen. Tasks of this type have been shown to be good proxies for spontaneous discourse and have been shown to be sensitive to speech changes in AD in previous studies [30-34]. The participant’s speech was recorded through the device’s microphone and analyzed via an automated speech analysis pipeline, generating variables reflecting different acoustic and linguistic properties of speech.

#### The Short-term Memory-Binding Test and Reading Task (by ViewMind)

Participants were asked to perform 2 cognitive tests, a short-term memory-binding test (STMBT) and a reading task while wearing a virtual reality headset with eye tracking (sampling rate of 120 Hz).

During the STMBT [35-37], participants were presented with a set of either 2- or 3-colored geometric shapes (Figure 2), depending on the cohort assignment at screening. The STMBT assesses the ability to temporarily hold bicolored objects whose colors have to be remembered either as individual features (baseline) or integrated within unified representations (binding).

The sentence corpus of the reading task comprised 40 regular sentences in Icelandic, which is the native language of all participants (eg, “Leifur heimsótti ættingja frá Evrópu í síðasta mánuði”; see the study by Fernández et al [38] for a description of a complete sentence corpus). The sentences comprised a well-balanced number of content and function words and had similar grammatical structure. Single sentences were presented at the centerline of the screen. The data used for analysis will be the x and y coordinates of eye movements together with time stamps and eye pupil diameter.

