**Methods:**

The Method for Evaluating Digital Endpoints in Alzheimer Disease study is an exploratory, cross-sectional, noninterventional study that will evaluate 10 digital technologies’ ability to accurately classify participants into 4 cohorts according to the severity of cognitive impairment and dementia. Moreover, this study will assess the psychometric properties of each of the tested digital technologies, including the acceptable range to assess ceiling and floor effects, concurrent validity to correlate digital outcome measures to traditional paper-and-pencil tests in AD, reliability to compare test and retest, and responsiveness to evaluate the sensitivity to change in a mild cognitive challenge model. This study included 50 eligible male and female participants (aged between 60 and 80 years), of whom 13 (26%) were amyloid-negative, cognitively healthy participants (controls); 12 (24%) were amyloid-positive, cognitively healthy participants (presymptomatic); 13 (26%) had mild cognitive impairment (predementia); and 12 (24%) had mild AD (mild dementia). This study involved 4 in-clinic visits. During the initial visit, all participants completed all conventional paper-and-pencil assessments. During the following 3 visits, the participants underwent a series of novel digital assessments.

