### Objectives

In light of the urgent need for improved efficacy end points for clinical drug trials and the rapid surge of promising digital technologies, the aim of the Method for Evaluating Digital Endpoints in Alzheimer Disease (MEDIA) study is to assess the psychometric properties, operational feasibility, and patient acceptance of 10 promising technologies for measuring cognition to be used as efficacy end points in future clinical drug trials. Each of the novel digital technologies will be compared against established paper-and-pencil end points in their ability to accurately classify participants into 4 cohorts of cognitive impairment and dementia severity. This paper describes the MEDIA study protocol and participant demographics, the role this study plays in the drug development process, and some of the limitations of the study.

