### Statistical Analysis

As this is an exploratory study, the sample size was chosen pragmatically to balance statistical and feasibility considerations. Data from 12 participants per cohort were considered to provide sufficient information for the study objectives [45].

Descriptive statistics (ie, mean, median, range, and SD) of the total score from each conventional end point and questionnaire will be reported by the cohort. Estimates of the between-cohort standardized differences in the corresponding total scores will be provided.

Digital technologies will produce ≥1 outcome variable (features) for each participant and assessment time. On the basis of these features, psychometric properties will be assessed: acceptable range (ceiling and floor effects), reliability (test-retest variability), validity (correlation to conventional end points), and responsiveness (change from test and retest to challenge) as appropriate. Various statistical rules for classifying participants into cohorts will be explored. The goodness of these rules will be assessed by calculating the sensitivity, specificity, positive predictive value, and negative predictive value. Receiver operating characteristics curves will be constructed to determine cutoff points with the best trade-off between sensitivity and specificity. Data from the participant feedback survey will be summarized descriptively.

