### Limitations

This exploratory methodology study has several limitations. Most notably, the small sample size necessitates findings to be confirmed in larger trials. Second, as this is a noninterventional study, it is difficult to establish sensitivity to change. One of the greatest risks that conventional end points pose to clinical drug development in neuroscience is the lack of sensitivity to changes and the possibility of missing important drug treatment effects. Hence, it is of utmost importance to demonstrate good assay sensitivity when studying novel digital end points to be implemented as efficacy measures in clinical trials. In this study, a benign cognitive challenge model was used in an attempt to assess the sensitivity to change of each digital end point. However, it is difficult to determine what challenge will be sufficient to reliably produce cognitive impairment in a cross-sectional study such as this one. Moreover, producing fatigue through late-night testing may not affect all cognitive domains to the same extent. Hence, the challenge model may affect participant performance on the various digital end points differently. In addition, as participants had no expectations of treatment benefits in this noninterventional study, it is possible that the digital end points would show different sensitivities to change in a clinical drug trial. Sensitivity to drug treatment effects cannot be fully evaluated until the digital end point is studied in a drug intervention trial. This is often the key validation data that novel digital end points are missing and is the most challenging data to acquire. This was a single-site study that provided limited information on how scalable the digital technologies are to multisite global trials and to what extent culture and language may be confounding factors. Finally, although the study included more men (33/50, 66%) than women (17/50, 34%), the proportions of men and women were, overall, similar across the 4 cohorts. It should also be noted that the education level was not evenly distributed across the cohorts; there was a greater number (and percentage) of participants with higher education in cohort 1 (9/13, 69%) than in cohort 2 (4/12, 33%), cohort 3 (4/13, 31%), and cohort 4 (3/12, 25%). As the education level may potentially be an important confounder, statistical analysis will be adjusted for it, as appropriate. Owing to the invasive procedures and sensitive biomarker information, there were no prospective CSF samples or PET imaging conducted in this noninterventional methodology study. Amyloid status was based on historical investigations that had to be aged <2 years. Historical reports were based on both CSF analysis (48/50, 96%) and PET imaging (2/50, 4%), and this study was not able to confirm any potential changes that may have occurred in amyloid status. Moreover, this study could not confirm any potential discrepancies between the 2 amyloid assessment procedures.

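### The memory-binding task used a stimulus version that depended on cohort, so its features cannot support classification between cohorts that saw different versions

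*Protocol article*

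**What the plan says.** The section on the STMBT and reading task states that "participants were presented with a set of either 2- or 3-colored geometric shapes (Figure 2), depending on the cohort assignment at screening". It adds that the test has a baseline condition, in which colors are remembered as separate features, and a binding condition, in which they are remembered as part of a whole object. It does not say which cohorts saw which version.

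The abstract's Methods paragraph says the study will "evaluate 10 digital technologies’ ability to accurately classify participants into 4 cohorts according to the severity of cognitive impairment and dementia". Under Objectives, each technology is to be "compared against established paper-and-pencil end points in their ability to accurately classify participants into 4 cohorts of cognitive impairment and dementia severity". Expected Findings lists the accuracy of this four-cohort classification first among the main results.

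Statistical Analysis covers all technologies in one set of rules: "Various statistical rules for classifying participants into cohorts will be explored", assessed by sensitivity, specificity, predictive values and ROC cutoffs. Ceiling and floor effects, test-retest reliability, correlation with conventional end points, and responsiveness are also planned, as appropriate. The only adjustment named is in Limitations: "As the education level may potentially be an important confounder, statistical analysis will be adjusted for it, as appropriate".

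**The concern.** The STMBT measures how much visual information a person can hold briefly, so the content of the display is part of the memory load. That content was chosen from the variable the technology is later asked to predict. A difference in accuracy, gaze or pupil measures between cohorts with different versions mixes cognition with stimulus. No cohort is described as having seen both versions, so the data cannot tell the two apart.

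The bias has no fixed direction. If features carry a trace of the version, a classifier can use it and appear to detect disease stage. If the more impaired cohorts had an easier version, their scores move toward those of healthier participants and a real deficit is hidden. Pooled ceiling and floor rates, and pooled correlations with conventional tests, would combine results from two different tests. A pooled reliability coefficient that uses between-person variance would also include the gap between versions. The road map in the Introduction uses methodology studies of this kind to decide which technologies advance to phase 2, so the result would be acted on.

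**Working it through.** The article gives no figure to reproduce here. It states no target accuracy, and the sample size of 12 per cohort is described as pragmatic. Two illustrations show what the confounding can do.

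**1. Upper bound: a rule that knows only the version**

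Inputs, from Participants: cohorts of 13 (controls), 12 (presymptomatic), 13 (predementia) and 12 (mild dementia); 13 + 12 + 13 + 12 = 50. Assumption: everyone in a cohort had the same version.

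- No information: always guess a largest cohort, 13/50 = 26%.
- Version known: within each version, guess its largest cohort. Accuracy = (largest cohort with version A + largest cohort with version B)/50.

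The mapping is not stated, so all seven possible splits are shown:

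| Split of cohorts | Correct | Accuracy |
|---|---|---|
| 1 vs 2, 3, 4 | 13 + 13 = 26 | 52% |
| 2 vs 1, 3, 4 | 12 + 13 = 25 | 50% |
| 3 vs 1, 2, 4 | 13 + 13 = 26 | 52% |
| 4 vs 1, 2, 3 | 12 + 13 = 25 | 50% |
| 1, 2 vs 3, 4 | 13 + 13 = 26 | 52% |
| 1, 3 vs 2, 4 | 13 + 12 = 25 | 50% |
| 1, 4 vs 2, 3 | 13 + 13 = 26 | 52% |

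The version alone about doubles four-cohort accuracy, to 50% or 52%, under every split. For a two-group contrast across versions it gives 100% sensitivity and specificity. Both figures require that the features fully reveal the version.

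**2. A single feature shifted by the version**

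Assume a normally distributed feature with equal variance. Let d be the true difference in SD between two cohorts with different versions, and s the shift in SD caused by the version. Then AUC = Φ((d + s)/√2). Both d and s are assumptions; the article gives neither.

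| True d | s = −1 | s = 0 | s = +1 |
|---|---|---|---|
| 0 | 0.24 | 0.50 | 0.76 |
| 0.5 | 0.36 | 0.64 | 0.86 |
| 1.0 | 0.50 | 0.76 | 0.92 |

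For example, d = 1 and s = +1 gives Φ(2/√2) = 0.92, and d = 1 and s = −1 gives Φ(0) = 0.50. A true one-SD difference can therefore vanish or be exaggerated, and no difference at all can look like useful discrimination. With a common version (s = 0), the AUC reflects only d.

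**3. Why adjustment does not help**

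Version is a function of cohort. In a model containing cohort, version adds no separate column, so its effect cannot be estimated. Adjusting for education leaves this untouched.

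**The case against.** Several points on the other side carry weight.

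- **The baseline condition may act as a control.** A within-person binding-minus-baseline contrast at one version could remove part of the version effect. Nothing shows that it removes all of it, and the article does not name it as the analysed feature. The only data statement is "The data used for analysis will be the x and y coordinates of eye movements together with time stamps and eye pupil diameter"; it closes the reading-task paragraph, and whether it also covers the STMBT is not explicit.
- **A restriction may exist elsewhere.** One generic paragraph covers 10 technologies, and task-level rules commonly sit in a full protocol or SAP. The lack of a restriction is therefore not itself the fault. The point rests on two things the article does state: the stimulus was set by cohort, and the technology is judged on classifying those cohorts.
- **The wording is ambiguous.** The version may refer to the number of shapes or the number of colors. Under either reading the stimulus differs by cohort.
- **Matching difficulty to ability is a reasonable way to avoid floor and ceiling effects.** It is, but the Introduction speaks of adaptive difficulty. Here difficulty was fixed by cohort, and no common scale linking the versions is described.

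A reader might also infer more than the article supports:

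- *Near-perfect four-cohort accuracy from the version alone.* The bound is 52%. Perfect separation applies only between the two groups of cohorts, and only if the features reveal the version. No plan to enter the version as a predictor is stated.
- *An unfair ranking among the 10 technologies.* The article compares each technology with paper-and-pencil end points and describes no ranking by classification accuracy.
- *All STMBT results are invalid.* They are not. Contrasts between cohorts with the same version stand, as do each person's changes from test to retest and to the evening challenge, provided the version set at screening was kept.

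**Conclusion.** The point holds for contrasts across stimulus versions. There, version and cohort are fully confounded, and STMBT classification, pooled range and pooled correlation results cannot be interpreted as measures of cognition. The most the version alone can contribute is perfect separation of the two groups of cohorts and 50% to 52% four-cohort accuracy, against 26%. The actual bias, and its direction, cannot be determined from the article, because neither the mapping of versions to cohorts nor the difference in difficulty is given. The conclusion assumes one version per cohort, which is the plain reading of the text.

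This should be fixed, but it does not threaten the study. It affects one of two tasks in one of 10 technologies, in an exploratory study whose findings, by its own Limitations section, need confirmation in larger trials.

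**What to change.** Data collection has ended, so the change is to the analysis and its reporting:

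1. State which cohorts received which version, and whether the versions differ in number of shapes or number of colors.
2. Use STMBT features for classification only between cohorts that shared a version.
3. Report STMBT range, reliability and correlations with conventional end points separately by version.
4. Base this technology's four-cohort classification result, and its comparison with paper-and-pencil end points, on the reading task alone.
5. Keep the within-person test-retest and challenge comparisons. If a binding-minus-baseline contrast is used, name it, and apply the same limits to it.

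The cost is a few sentences and no new data. The downside is that the STMBT gives no result for contrasts across versions, where a result could not be interpreted anyway, and that results by version rest on smaller groups.

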#### Retinal Imaging (Retia by NeuroVision)

Using an adapted ophthalmoscope (ophthalmoscope specification tailored for blue-light confocal autofluorescent imaging, with excitation illumination at 450 nm using a single flash light-emitting diode, emissions capture at ≥500 nm, and pixel resolution equivalent to 9 µm on the retina), confocal images of the retina were acquired at visit 2. After the administration of drops for eye pupil dilation (tropicamide 1% weight/volume) to the participant’s eyes to dilate the pupil to at least 3.5 mm in diameter, a series of autofluorescent images of the retina were acquired—nominally 18 images per eye. The entire noninvasive imaging procedure takes approximately 15 to 30 minutes. The participants’ raw image stack is processed by the automated software analysis package to assess the presence, size, position, shape, and other attributes of retinal autofluorescent spots. As the number of autofluorescent spots on the retina was correlated with the larger retinal amyloid burden in participants with AD versus controls [39,40], the likelihood of positive brain amyloid pathology, as determined by CSF sampling or amyloid PET imaging, will be calculated.

#### Digital Clock-Drawing and Cognitive Tablet-Based Drawing Tests (DCTclock by Linus Health)

##### DCTclock

DCTclock [41,42] is a digitized version of the standard rapid and noninvasive pen-and-paper neuropsychological clock-drawing test. The test involves participants drawing 2 clock faces on a piece of paper with a digital pen that precisely tracks and records the drawing behavior. The time-stamped positional data (x and y coordinates and time stamps) generated during this assessment are analyzed using proprietary machine learning algorithms that evaluate hundreds of features captured by the drawing process and the final output. By comparing test results with normative data, the system then determines whether the test is within normal limits and provides a detailed breakdown of performance on the various cognitive tasks evaluated during the test.

##### Cognitive Tablet-Based Drawing Tests

Participants were asked to complete a pretest assessment to familiarize themselves with the tablet and five short tablet-based drawing tests: (1) pretest, (2) pathfinding test, (3) symbol test, (4) trails test, and (5) tracing test. The pretest exercise involves copying waves. It was administered before completing the other tablet tests with the only goal of making the participant comfortable with drawing using the Apple Pencil and the iPad. In the pathfinding test, participants were asked to complete a series of mazes of increasing difficulty as quickly and accurately as possible. The symbol test comprises a key of 9 symbol-digit pairs followed by empty boxes with symbols on the top. Under each symbol, the participants must write down the corresponding symbol as fast as possible. In the trails test, the participant was instructed to connect a set of circles as quickly as possible, with the first part connecting numbers only and the second part connecting alternating numbers and letters. In the tracing test, the participant was prompted to trace a series of spirals and circles, first with their dominant hand and then with their nondominant hand. Expected features for further analysis are the time to finish a task, total strokes needed, and efficiency of drawing.

